## Abstract

**Background:**

The efficacy and safety of Lisdexamfetamine dimesylate (LDX) in the treatment of moderate to severe binge eating disorder (BED) has been demonstrated in multiple randomised clinical trials. Despite this, little is known about how LDX acts to improve binge eating symptoms. This study aims to provide a comprehensive understanding of the neural mechanisms by which LDX improves symptoms of BED. We hypothesise that LDX will act by normalising connectivity within neural circuits responsible for reward and impulse control, and that this normalisation will correlate with reduced binge eating episodes.

**Methods:**

This is an open-label Phase 4 clinical trial of LDX in adults with moderate to severe BED. Enrolment will include 40 adults with moderate to severe BED aged 18–40 years and Body Mass Index (BMI) of 20–45 kg/m^2^, and 22 healthy controls matched for age, gender and BMI. Clinical interview and validated scales are used to confirm diagnosis and screen for exclusion criteria, which include comorbid anorexia nervosa or bulimia nervosa, use of psychostimulants within the past 6 months, and current use of antipsychotics or noradrenaline reuptake inhibitors. Baseline assessments include clinical symptoms, multimodal neuroimaging, cognitive assessment of reward sensitivity and behavioural inhibition, and an (optional) genetic sample. A subset of these assessments are repeated after eight weeks of treatment with LDX titrated to either 50 or 70 mg. The primary outcome measures are resting-state intrinsic connectivity and the number of binge eating episodes. Analyses will be applied to resting-state fMRI data to characterise pharmacological effects across the functional connectome, and assess correlations with symptom measure changes. Comparison of neural measures between controls and those with BED post-treatment will also be performed to determine whether LDX normalises brain function.

**Discussion:**

First enrolment was in May 2018, and is ongoing. This study is the first comprehensive investigation of the neurobiological changes that occur with LDX treatment in adults with moderate to severe BED.

**Trial registration:**

ACTRN12618000623291, Australian and New Zealand Clinical Trials Registry URL: https://www.anzctr.org.au/Trial/Registration/TrialReview.aspx?id=374913&isReview=true. Date of Registration: 20 April 2018.

## Background

Binge Eating Disorder (BED) is an eating disorder characterised by recurrent episodes of excessive eating with a sense of lack of control over eating. These recurrent episodes need to occur at least once a week for 3 months to meet the diagnostic criteria of the *Diagnostic and Statistical Manual of Mental Disorders* (5th ed) [1]. It is the most common type of eating disorder in Australia, with an estimated 3-month point prevalence of 5.6%, compared with 0.5% for anorexia nervosa and 0.7% for bulimia nervosa [2]. It is also distinct from obesity, whereby obese people with BED are reported to have greater body image disturbance, lower self-esteem, and more psychiatric comorbidity with mood and anxiety disorders, compared to those without [3, 4].

Current evidence suggests that pathologic overeating in BED may be related to dysfunction of the dopamine (DA) and noradrenaline (NA) systems, increased reward sensitivity, and impulsivity towards food intake [5]. For instance, in a positron emission tomography (PET) study, high Body Mass Index (BMI) individuals with BED were found to have significantly increased DA levels in the caudate and putamen in response to food stimuli, relative to high BMI individuals without BED [6]. This significantly correlated with binge eating severity but not with BMI. Functional magnetic resonance imaging (fMRI) studies have broadly shown dysfunction in the fronto-striatal regions relating to reward and inhibition [7–12]. Further, those with BED may have impaired flexibility in reward-based decision making, with reduced activation in regions implicated in goal-directed action and evaluation of reward-based choice such the bilateral anterior insula and ventro-lateral prefrontal cortex [13]. Despite these important insights into the neuropathophysiology of BED, more studies are required to better understand neural dysfunction in BED, and how pharmacotherapies influence these systems to reduce BED symptoms.

In early 2015, the United States Food and Drug Administration (FDA) approved lisdexamfetamine dimesylate (LDX) (Vyvanse) for the treatment of moderate to severe BED in adults. Although psychotherapy is still the first-line treatment, pharmacological treatments such as LDX can be useful for those who are non-responsive to psychotherapy or for those in locations where psychotherapy is unavailable. LDX is a central nervous system stimulant, which is hydrolysed in the blood to yield long-acting d-amphetamine [14]. It increases DA and NA levels by inhibiting reuptake into the presynaptic neuron and therefore increasing the release of these monoamines into the extra neuronal space. The efficacy and safety of LDX in the treatment of moderate to severe BED for up to 12 months has been demonstrated in multi-site, double-blind, randomised, placebo-controlled clinical trials [15–19]. While reported to be generally safe, common adverse events include dry mouth, headache and insomnia [15, 16, 18], in line with other long-acting psychostimulant medications.

Despite its demonstrated efficacy for moderate to severe BED, the exact mechanism of action by which LDX improves binge eating symptoms remains unknown. Behaviorally, LDX has been shown to improve impulse control in people with BED and Attention Deficit Hyperactivity Disorder (for which LDX is also indicated) [20–22]. It is presumed that, similar to other psychostimulants, LDX improves impulse control by modulation of the prefrontal cortex, a region involved in self-regulation and inhibitory control [23, 24]. To date however, no studies have been published on the neural effects of LDX in moderate to severe BED.

It is widely recognised that cognition and behaviour arise from the dynamic interactions of distributed brain areas operating in networks. These large-scale networks can be imaged during functional tasks that evoke their activity, or during rest, when they tend to produce highly synchronised, very low frequency neuronal oscillations [25]. Analysis of resting-state functional magnetic imaging (rs-fMRI) can reveal much about the innate organisation of the brain, by demonstrating how brain regions, or nodes, are organised within networks, and how various networks are intrinsically connected with one another [26]. Applying a connectomic approach increases potential for providing new insights into the neural mechanisms of pharmacotherapy by providing comprehensive descriptions of these intrinsic connectivity patterns [27, 28].

There are currently no studies published on intrinsic connectivity patterns in BED relative to controls. As such, it is difficult to hypothesise precisely how LDX will effect neural connectivity in this group. Given the known dysfunction in the fronto-striatal regions relating to reward and inhibition in BED, it is assumed however that effective treatment with LDX will “normalise” activity and connectivity within these networks. We will also be able to examine relationships between treatment-driven neural changes and a large range of symptom measures and objective laboratory-based measures of cognition. These secondary meaures may also help to determine whether LDX exerts beneficial effects more broadly to non-food inhibitory control and other general cognitive improvements.

The primary aim of this study is to provide a comprehensive understanding of the neural mechanisms by which LDX improves symptoms of BED. We hypothesise that LDX will act by normalising connectivity within and between brain circuits responsible for reward and impulse control. Further, we hypothesise that a reduction in binge eating behaviours will correlate with normalised activity and connectivity of brain regions within reward and impulse control networks. Secondary aims include examining treatment-related changes in cognitive performance and other self-reported measures of symptoms and behaviour.

## Method

### Participants

Approximately 40 participants with BED and 22 healthy matched controls will be recruited into the study. Both BED and control participants must be between 18 to 40 years of age (inclusive), and have a BMI between 20 to 45 kg/m^2^ (inclusive). BED participants are required to have a diagnosis of moderate to severe BED. This is based on Module I of the *Structural Clinical Interview for DSM-5 Research Version* (SCID-5-RV) [29]. Consistent with LDX efficacy studies [18, 19], moderate to severe BED severity requires a minimum of three days of binge eating per week in the past month and a minimum score of 4 on the *Clinical Global Impression – Severity* scale (CGI-S) [30], a clinician-determined summary measure of a patient’s global functioning. The *MINI International Neuropsychiatric Interview Version 7.0.2 for DSM-5* [31] (MINI) is also used to assess comorbid psychiatric disorders to determine eligibility and better characterise the cohort. The full inclusion and exclusion criteria for BED and control participants are listed in Tables 1 and 2.

**Table 1 Tab1:** Inclusion and exclusion criteria for BED participants

Criteria	List
Inclusion	• Age 18–40 years.
	• BED diagnosis, confirmed by the eating disorders module of the Structured Clinical Interview for DSM-5.
	• Moderate to severe BED, defined as the presence of binge eating frequency of ≥3 days/week in the month prior to the baseline assessment and a score of ≥4 on the clinical global impressions severity scale.
	• BMI of 20 – 45 kg/m^2^.
	• A study doctor has verified that it is medically and psychiatrically safe for their patient to commence LDX.
	• Fluent in English.
	• Have provided written informed consent.
Exclusion	• History of psychosis or mania.
	• Pregnant or breast-feeding women.
	• Current therapy with antipsychotics or noradrenaline reuptake inhibitors.
	• Current therapeutic intervention specific to treating eating behaviours and/or cognitions.
	• Cardiovascular disease, hypertension, use of monoamine oxidase inhibitors, or any other contraindications for psychostimulants.
	• History of substance abuse/dependence (excluding nicotine).
	• Previous suicide attempts or current suicidal ideation.
	• Known medical condition, disease or neurological disorder which might, in the opinion of investigator/s, interfere with the assessments to be made in the study or put BED patients at increased risk when exposed to optimal doses of the drug treatment.
	• Use of a psychostimulant in the 6 months prior to the study.
	• Inability to tolerate the MRI scanner due to physical or psychological factors.
	• History of physical brain injury or blow to the head that resulted in loss of consciousness for at least 10 min.

**Table 2 Tab2:** Inclusion and exclusion criteria for control participants

Criteria	List
Inclusion	• Age 18–40 years.
	• BMI of 20 – 45 kg/m^2^.
	• Fluent in English.
	• Have provided written informed consent.
	• Current or previous diagnosis of an eating disorder or any other psychiatric diagnosis, including substance dependence.
Exclusion	
	• Pregnant or breast-feeding women.
	• Inability to tolerate the MRI scanner due to physical or psychological factors.
	• Known medical condition, disease or neurological disorder which might, in the opinion of investigator/s, interfere with the assessments to be made in the study or put subjects at increased risk.
	• History of physical brain injury or blow to the head that resulted in loss of consciousness for at least 10 min.
	• Prior treatment with any stimulant medication.

Participants are being recruited via referral by participating clinicians or self-referral due to online advertisements through Facebook, volunteer job sites, and webpages of universities in the Sydney metropolitan area.

### Overall study design

This study is a repeated-measures pre-post treatment design. Repeated-measures data from a control group is being collected at week 0 and week 8 for normative comparisons. Figure 1 outlines the timeline of events.

**Fig. 1 Fig1:**
[figure not shown]
Study design and timeline of events for participants with Binge Eating Disorder (BED) and healthy controls

#### Screening

Potentially eligible participants complete an online screening questionnaire, followed by a more detailed telephone screen with a researcher. BED participants who appear eligible following the telephone screen undergo a medical history and safety assessment with a study clinician. The relevant prescription authority approvals are sought for each potential BED participant.

#### Pre-treatment baseline session (week 0)

During a 6 h testing session, all participants complete 1. a clinical interview and health check, 2. functional, structural and resting-state magnetic resonance imaging (MRI), 3. several self-report questionnaires relating to behavioural, attitudinal, cognitive and affective aspects of eating-disorder psychopathology, 4. a series of cognition-based tasks, and 5. a saliva sample for genetic analysis (optional). BED participants are provided with self-monitoring sheets and a script for their first course (4 weeks) of medication.

#### Clinical safety checks (week 2 and week 4)

After 2 weeks of treatment, BED participants have their blood pressure and heart rate measured by a study researcher or their General Practitioner. Participants are instructed to commence the increased dose of 50 mg/day if it is determined to be safe by the study clinician. After 4 weeks of treatment, participants meet with the study clinician for a comprehensive safety and dose check, including vitals, weight, drug compliance, adverse events and frequency of binge eating episodes. The clinician assesses the participants’ responsiveness to medication and symptom severity and determines whether the dose should remain at 50 mg/day or increase to 70 mg/day. Participants are then provided with a script for their remaining course (4 weeks) of medication. Participants are instructed to report any adverse effects or side effects as soon as possible, and may be advised to reduce the dose or stop the medication at any time.

#### Post-treatment session (week 8)

BED participants return the self-monitoring sheets provided during the baseline session and any unused tablets at the follow-up session. The majority of the assessments undertaken at session 1 are repeated at session 2 for both BED and control participants. The assessments/tasks that are not performed in session 2 are the SCID-5-RV and MINI, structural MRI and diffusion weighted imaging (DWI), and the Wechsler Test of Adult Reading [32] (WTAR). This session takes approximately 5 h to complete.

### Intervention

BED participants complete an 8 week course of LDX. The dose schedule for LDX is based on existing clinical practice and efficacy literature [18, 19]. All participants commence with 30 mg/day of LDX, and are advised to take it at the same time each morning. Participants are provided with self-monitoring sheets to help track their medication compliance.

After 2 weeks, participants will increase their dose to 50 mg/day if there are no abnormal changes to their blood pressure and heart rate. After 4 weeks, participants may continue with 50 mg/day or increase to 70 mg/day depending on their responsiveness to medication and symptom severity. Participants will remain on this dosage for another 4 weeks. At the week 8 follow-up session, participants will be required to return the completed self-monitoring sheets and any unused tablets. Participants with a compliance rate of less than 60% following a count of unused tablets will be viewed as non-compliant, and their data will be excluded from analysis.

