### Supplementary outcomes

Comparisons will be made between the pre-treatment BED group and healthy controls on the full range of measures to better characterise symptoms, cognition and neural function in BED.

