### Data analysis

Only the data from individuals with a medication compliance rate of ≥60% will be included in primary outcome analyses. For all analyses, a *p* value of < 0.05 will be considered statistically significant and relevant corrections for multiple comparisons will be applied.

Framewise displacement—movement of the head from one volume/timepoint to the next—and scaled signal intensity differences between contiguous volumes, will be calculated for each rs-fMRI time series during the quality control process. Temporal masks will be applied to censor volumes including motion, and participant data will be excluded from analyses if more than 1/3 of the time course data requires temporal masking.

Functional connectomics involves the study of brain connectivity, first by identifying the nodes (distinct brain regions) and subsequently estimating the functional connections (network edges) between these nodes [51]. Both voxel-wise and brain atlas parcellation approaches (e.g. Gordon parcellations) [52] will be utilised to designate nodes. Data-driven, whole-brain analyses using methods such as multivariate distance matrix regression [53] and network based statistics [54] will then be applied to rs-fMRI data to characterise pharmacological effects across the functional connectome, and assess correlations with symptom measure changes. Using a similar approach to Yang et al. [55], the results of data-driven analyses will be followed up using seed-based functional connectivity analyses. Connectomic measures will be computed for BED participants at baseline and post-treatment. A paired-sample t-test will be performed to compare baseline and post-treatment connectivity profiles to confirm the treatment effect. To examine any normalisation effects of LDX in BED participants, two independent sample t-tests will be conducted to compare functional connectivity between healthy controls, and the BED group at baseline and post-treatment, respectively. To examine the association of changes in functional connectivity and clinical improvement, we will correlate change scores (Δ = BED post-treatment – BED baseline) of functional connectivity with changes in the number of binge-eating episodes.

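### The 60% tablet-count exclusion is stated with two scopes, selects the binge-eating outcome on a post-baseline variable, and does not secure drug exposure at the week-8 scan

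*Protocol article*

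**What the plan says.** Two sections of the protocol article state the rule. Under Intervention, anyone whose compliance is "less than 60% following a count of unused tablets will be viewed as non-compliant, and their data will be excluded from analysis", with no limit to particular outcomes. Under Data analysis: "Only the data from individuals with a medication compliance rate of ≥60% will be included in primary outcome analyses". For secondary outcomes, Data analysis promises only an approach similar to that for the primary ones.

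Compliance is established once, at the end: "BED participants return the self-monitoring sheets provided during the baseline session and any unused tablets at the follow-up session". Medication is supplied as two four-week scripts, the second after the week-4 check: "Participants are then provided with a script for their remaining course (4 weeks) of medication". Under Clinical safety checks, participants who report adverse effects "may be advised to reduce the dose or stop the medication at any time".

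The primary outcomes, measured before and after treatment, are resting-state connectivity and binge-eating episodes. Separately, under Supplementary outcomes, "Comparisons will be made between the pre-treatment BED group and healthy controls on the full range of measures".

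**The concern.** There are three separate problems.

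- **Scope.** The two statements define different populations for every secondary and supplementary analysis. Under the Intervention wording, a participant's week-0 scan and questionnaires drop out of the baseline comparison with controls because of tablets not taken later. Later compliance has no bearing on a pre-treatment measurement.
- **Selection.** Compliance is observed after treatment starts. People who stop because of side effects or lack of benefit can fall below 60% and leave the binge-episode outcome even if they attend week 8 and supply data. The article describes no analysis that includes them.
- **Exposure.** The justification for a compliance set in a mechanistic imaging study is that it contains people who were on drug when measured. A cumulative count over the whole course does not establish that, and the article states no condition on recent dosing.

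At stake are an observed binge reduction that may be too large, an imaging contrast that may be diluted, and a baseline comparison that may lose usable data. Selection also reaches the mechanistic hypothesis, because change in binge episodes is correlated with change in connectivity in the same selected set.

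**Working it through.** **Inputs.** From Intervention: "BED participants complete an 8 week course of LDX", taken once each morning, so 8 × 7 = 56 prescribed doses; threshold 60%. From Sample size calculation: 40 BED participants recruited, about 35 analysable, effect size 0.5, two-sided alpha 0.05, power about 80%. From Data analysis: paired t-test.

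**The plan's own figure.** Paired-t power uses the noncentral t with n − 1 degrees of freedom and noncentrality d√n. With n = 35 and d = 0.5, the noncentrality is 0.5 × √35 = 2.96 and power is 0.82. This agrees with the stated 80%; the smallest n reaching 80% is 34. The sample size is not in dispute.

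**Scope, side by side.**

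| Analysis | Intervention wording | Data analysis wording |
|---|---|---|
| Primary outcomes | below 60% excluded | below 60% excluded |
| Secondary outcomes | excluded | not covered (similar approach) |
| Baseline BED versus controls | excluded | not excluded |

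**What the threshold means.** The denominator is not stated, so take both readings, with the scan on day 56.

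- *Prescribed doses:* 0.60 × 56 = 33.6, so 34 doses qualify. Stopping after day 33 gives 33/56 = 58.9% (excluded). Stopping after day 34 gives 34/56 = 60.7% (kept, with 56 − 34 = 22 days off drug). Stopping after day 42 gives 75% (kept, 14 days off drug).
- *Dispensed tablets:* someone who takes the first script, stops at week 4 and never fills the second has taken 28 of 28 = 100% and is kept after 28 days off drug. On the prescribed-dose reading the same person scores 28/56 = 50% and is excluded.

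**Illustration 1: binge episodes.** Suppose k of 40 are excluded, all 40 have week-8 data, and the k had zero mean change. The compliant-set mean then exceeds the all-treated mean by the ratio 40/(40 − k):

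- k = 1: 40/39 = 1.026
- k = 3: 40/37 = 1.081
- k = 5: 40/35 = 1.143

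**Illustration 2: imaging.** Suppose k of the 35 analysed are off drug at the scan with zero mean change and the SD is unchanged. Then d = 0.5 × (35 − k)/35:

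| k | d | power |
|---|---|---|
| 0 | 0.500 | 0.82 |
| 1 | 0.486 | 0.80 |
| 3 | 0.457 | 0.75 |
| 4 | 0.443 | 0.72 |
| 6 | 0.414 | 0.66 |

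**Illustration 3: cost of including everyone scanned.** Adding 1 to 5 zero-change non-compliers to a fully exposed 35 gives d = 0.5 × 35/N. Power is 0.81 at N = 36 and 0.77 at N = 40.

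**How much of the allowance could be non-compliance.** The drop from 40 to 35 is explained by 98% retention and 2 to 3 losses to motion: 40 × 0.98 − 2 = 37.2 and 40 × 0.98 − 3 = 36.2. About 1 to 2 places remain for anything else. Exclusions of that size would put Illustration 1 at 40/39 to 40/38, or about 3% to 5%.

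**The case against.** The strongest defence is the study's purpose. The primary aim is mechanism, and the Discussion says that the trial is not meant to establish efficacy and cannot attribute change to LDX alone. Restricting a mechanistic analysis to exposed people is reasonable. In Data analysis the paired test concerns connectivity, and binge change enters through its correlation with connectivity change. This stands for imaging, and a compliance set should be kept there. It does not fully cover binge episodes, which are named as a primary outcome in their own right.

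Second, the Data analysis wording can be read as the operative rule, with the Intervention sentence a loose summary. On that reading the baseline comparison loses nobody. That is plausible, but the text does not say which sentence governs.

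Third, there are safeguards: the week-4 visit checks drug compliance, self-monitoring sheets are collected, and a full protocol may hold scan-day dosing instructions that an article would omit. These reduce the worry, but the week-4 check cannot speak for weeks 5 to 8.

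Fourth, the magnitudes are hypothetical. A reader might infer that the binge result is inflated by 14%, or that imaging power is really 0.72 or 0.66. The article supports neither. It gives no rate of non-compliance or of being off drug at the scan, and it names non-drug influences, such as the diary and clinician contact, that could produce change in people not taking tablets. The 14% figure also spends the whole five-person allowance on non-compliance, although retention and motion account for most of it. Nor is it established that everyone who stops before day 34 is dropped, since that depends on the unstated denominator.

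**Conclusion.** The concern holds in a limited form. The mismatch in scope is plain from the text. Selection of the binge-episode outcome on a post-baseline variable also follows from the rule. Its direction is probably toward a larger reduction, but this is not certain, and nothing in the article shows that those retained are responders. The gap in exposure at the scan is a possibility shown by arithmetic, not a documented occurrence, and it arises on either reading of the denominator: up to 22 final days missed on prescribed doses, or 28 in the unfilled-script case on dispensed tablets.

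The ranges, about 3% to 14% for the binge reduction and power of 0.80 to 0.66 against 0.82 for imaging, rest on assumed counts and zero change in the affected people. They show sensitivity and are not estimates. The points merit correction because the remedy is cheap; they do not undermine the design or the sample size.

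**What to change.** 1. Make Intervention and Data analysis state the same scope, including for secondary outcomes, and say that compliance does not affect inclusion in the baseline BED-control comparisons.
2. Report binge-episode change in all BED participants who started LDX and have week-8 data, whatever their compliance, alongside the 60% set. Note that people without week-8 data remain missing, so this reduces the selection but does not remove it.
3. Keep a compliance set as the mechanistic analysis of resting-state fMRI. State its denominator, and base it on the period up to the scan, using the self-monitoring sheets together with the tablet count. Add a sensitivity analysis of all scanned participants.

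The cost is revised wording, a second binge-eating population, a redefined imaging set and one sensitivity run, from data already collected. The timing of missed doses would rest on self-report, because a week-8 count cannot date them. The imaging set still selects on post-baseline behaviour, which is acceptable for a mechanistic question if labelled as such. The all-treated binge estimate will probably be slightly smaller. None of this requires a change to dosing or to the handling of adverse effects.
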